# The redox-dependent regulation of satellite cells following aseptic muscle trauma (SpEED): study protocol for a randomized controlled trial

**DOI:** 10.1186/s13063-019-3557-3

**Published:** 2019-07-31

**Keywords:** Muscle stem cells, Redox potential, Antioxidants, Cell signaling, Tissue regeneration

## Abstract

**Background:**

Muscle satellite cells (SCs) are crucial for muscle regeneration following muscle trauma. Acute skeletal muscle damage results in inflammation and the production of reactive oxygen species (ROS) which may be implicated in SCs activation. Protection of these cells from oxidative damage is essential to ensure sufficient muscle regeneration. The aim of this study is to determine whether SCs activity under conditions of aseptic skeletal muscle trauma induced by exercise is redox-dependent.

**Methods/design:**

Based on the SCs content in their vastus lateralis skeletal muscle, participants will be classified as either high or low respondents. In a randomized, double-blind, crossover, repeated-measures design, participants will then receive either placebo or *N*-acetylcysteine (alters redox potential in muscle) during a preliminary 7-day loading phase, and for eight consecutive days following a single bout of intense muscle-damaging exercise. In both trials, blood samples and muscle biopsies will be collected, and muscle performance and soreness will be measured at baseline, pre-exercise, 2 and 8 days post exercise. Biological samples will be analyzed for redox status and SCs activity. Between trials, a 4-week washout period will be implemented.

**Discussion:**

This study is designed to investigate the impact of redox status on SCs mobilization and thus skeletal muscle potential for regeneration under conditions of aseptic inflammation induced by exercise. Findings of this trial should provide insight into (1) molecular pathways involved in SCs recruitment and muscle healing under conditions of aseptic skeletal muscle trauma present in numerous catabolic conditions and (2) whether skeletal muscle’s potential for regeneration depends on its basal SCs content.

**Trial registration:**

ClinicalTrials.gov, ID: NCT03711838. Registered on 19 Oct 2018.

**Electronic supplementary material:**

The online version of this article (10.1186/s13063-019-3557-3) contains supplementary material, which is available to authorized users.

## Background

Skeletal muscle stem cells (satellite cells – SCs) are required for muscle repair, remodeling and growth [1]. Under conditions of increased transcriptional activity, such as in response to skeletal muscle injury, SCs are activated to promote healing [2]. SCs can be identified by their location (beneath the basal lamina of myofibers) and by the expression of transcriptional proteins, such as paired box protein (Pax7). Each stage of the regeneration process is partly controlled by myogenic regulatory factors (MRFs) which include myogenic factor 5 (Myf5), myogenic determination factor (MyoD), myogenin and myogenic factor 4 (Myf4), all orchestrating skeletal muscle’s myogenic programming [3, 4].

Recent data suggest a redox-regulated link between SCs and myogenesis [5]. Muscle injury triggers the nuclear factor kappa-light-chain-enhancer of activated B cells (NF-kB)-mediated apoptosis to control stem-cell survival and maintain stemness [6]. SCs’ antioxidant reserves protect these cells from oxidative damage whereas antioxidant enzymes, glutathione peroxidase 3 (GPX-3), superoxide dismutase 2 (SOD-2) and thioredoxin (Trx-1) regulate the homeostatic programming of quiescent SCs [7, 8]. Redox-sensitive signaling pathways, such as Notch and Wnt/β-catenin, are also critical for multiple stages of myogenesis including activation and proliferation of SCs. Interestingly, several Wnt proteins have been shown to regulate SCs activation, proliferation and differentiation [9, 10].

Skeletal muscle trauma is observed in numerous catabolic conditions, characterized by elevated proteolysis and muscle wasting, such as cancer, cachexia and muscular dystrophy, which result in physical capacity impairment and a deteriorated quality of life [11, 12]. In the absence of SCs, injured skeletal muscle abolishes its ability to regenerate or regenerates very poorly in response to muscle injury [13]. Flow cytometric analysis in isolated SCs revealed that the number of Pax7^+^ cells/mg of muscle in G2/M, G0/G1 and S phases of the cell cycle increased by 202%, 32% and 59%, respectively, at 24 h post injury [14]. Under these conditions, SCs rapidly migrate to the injured area, differentiate into mature myoblasts and contribute to myofiber repair [15]. Exercise-induced muscle damage (EIMD) results in an aseptic muscle microtrauma and a pronounced inflammatory cascade characterized by leukocyte immobilization, macrophage infiltration, cytokine production and increased oxidative stress (OXS) [16, 17]. A study incorporating a muscle damage protocol (300 maximal eccentric contractions) on an isokinetic dynamometer, showed an increase in SCs content even at 180 h post exercise [18]. These marked similarities between aseptic EIMD and trauma makes eccentric exercise a valuable model to investigate the redox-dependent intracellular regulation of SCs involvement in skeletal muscle’s healing potential.

Only two studies have examined the effectiveness of antioxidant supplementation on skeletal muscle healing and the inflammatory response in primary cultured cells and rat gastrocnemius muscle demonstrating that polyphenol administration enhances SCs activation and evokes an earlier appearance of M2 macrophages promoting an anti-inflammatory phenotype [19, 20]. However, no studies have investigated, so far, the effect of redox status perturbations on SCs responses and myogenic potential following aseptic trauma in human skeletal muscle. A powerful antioxidant that has been in clinical and sports performance practice for several decades is *N*-acetylcysteine (NAC). NAC is a thiol donor, non-specific antioxidant with a binary antioxidant role: Firstly, NAC directly scavenges a number of reactive oxygen species (ROS) and secondly, it produces reduced cysteine (Cys) by deacetylation, which supports the biosynthesis of endogenous reduced glutathione (GSH) via the activity of γ-glutamylcysteine synthase [21]. GSH plays a pivotal role in cellular metabolism and especially in terms of stem cells’ oxidative defense, activity, survival and self-renewal under conditions of increased OXS and ROS production [22]. Low to moderate ROS levels control physiological cellular signaling pathways and facilitate muscle growth and development while high ROS levels impair myogenesis and cause cell death through apoptotic and/or necrotic mechanisms (e.g., NF-kB signaling) [23]. We hypothesize that NAC administration following aseptic muscle trauma, characterized by severe inflammation and high levels of ROS, will alleviate the increase in oxidative stress by decreasing ROS activity levels, resulting in an optimal intracellular redox environment, favoring the activity (activation, proliferation, differentiation and fusion) of SCs and thus facilitating muscle’s regenerative process and adaptation following muscle injury. Thus, the objectives of this clinical trial are to examine the effects of redox status perturbation (via NAC administration) on the intracellular pathways responsible for SCs responses following aseptic muscle trauma induced by damaging exercise.

## Methods/design

### Study overview and design

The methods and ethics of the present study have been approved by the Institutional Review Board of the University of Thessaly (ref. number 1387) and procedures are in accordance with the Declaration of Helsinki, as revised in 2013. The SpEED study incorporates a randomized, two-trial (NAC vs placebo), cross-over, double-blind, repeated-measures design. Participants who will fulfill the inclusion criteria will have their body mass, height, resting metabolic rate (RMR), body composition, muscle strength, soreness and maximal oxygen consumption (VO_2max_) measured. Since protein and antioxidant consumption as well as systematic physical activity (PA) and/or exercise may affect SCs responses and/or redox status, participants’ daily nutrient intake (via a 7-day diet recall with emphasis on protein and antioxidant intake) and PA levels (via accelerometry instrumentation) will be monitored for a week before the inception of the study [24–26]. Then, a 2-week adaptation period (only before the first trial) will be applied to adjust (through a balanced diet, using RMR values and daily energy expenditure measurements) protein and antioxidant intake at the levels required by current Recommended Dietary Allowances (RDAs) (0.8–1 g of protein/kg/day; 900 mg/day of vitamin A; 90 mg/day of vitamin C; 600 IU/day of vitamin D; 15 mg/day of vitamin E; 11 mg/day of zinc; 400 mg/day of magnesium and 55 mg/day of selenium) [27, 28]. This dietary protocol will be designed and implemented by a registered dietician. During the same time-frame, familiarization with experimental procedures will be provided.

Evidence exists that skeletal muscle growth and myogenic potential is directly related to its basal SCs content [24, 29]. As such, volunteers will provide a resting (they will abstain from any exercise or intense PA for at least 5 days prior to sampling) muscle biopsy sample (baseline sampling) from their vastus lateralis muscle (of their dominant limb) and based on its SCs content will be stratified to either high (HR) or low (LR) respondents. Participants will be stratified as HR or LR using a K-means cluster analysis. Blood sampling and performance measurements will also be performed at baseline.

Following stratification to the HR and LR groups, volunteers of each group will then perform two trials in a randomized order: (1) NAC ingestion and (2) placebo ingestion. NAC or placebo will be consumed before (a 7-day loading phase) and after (immediately post exercise and for eight consecutive days thereafter) an intense eccentric exercise protocol. During both trials, participants will follow the balanced daily dietary protocol of the adaptation period. However, daily dietary intake will be recorded and analyzed during each trial in an attempt to minimize deviations from the prescribed diet. A 4-week washout period will be implemented between trials (dietary intake during this period will also be adjusted according to that applied during the adaptive period). During the entire experimental period, participants will be asked to abstain from any strenuous PA or exercise. Muscle biopsies and blood samples will be collected after overnight fasting before the exercise protocol (pre-exercise sampling) as well as at 2 and 8 days post exercise. Muscle strength and delayed onset of muscle soreness (DOMS) will be evaluated at the same time points. All measurements and collection of biological samples will be performed at the same time of day, in both trials, to prevent circadian rhythm variations. Figure 1 shows the Consolidated Standards of Reporting Trials (CONSORT) diagram of the study and Fig. 2 illustrates the experimental flowchart for the clinical trials.

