**Fig. 2 Fig2:**
[figure not shown]
The experimental flowchart for the clinical trials

The primary outcomes of the study are the SCs-specific markers measured in muscle (Pax7^+^, MyoD^+^ cells per type I/II myofibers), the macrophages’ markers measured in muscle (cluster of differentiation 11b marker (CD11b^+^), cluster of differentiation 206 marker (CD206^+^) cells per myofiber), the myogenesis-related markers measured in muscle (Myf5, MyoD, myogenin, MRF4 and myostatin mRNA expression levels), the cell signaling markers measured in muscle (GPX-3, SOD-2, Trx-1, insulin-like growth factor 1 (IGF-1), Notch1, Wnt3 protein expression levels), and the oxidative stress markers measured in muscle (GSH, oxidized glutathione (GSSG), protein carbonyls (PC) and malondialdehyde (MDA)). The secondary outcomes are the oxidative stress markers measured in blood (total antioxidant capacity (TAC) in serum, GSH, GSSG, catalase (CAT) and hemoglobin (Hb) in red blood cell lysates), and the inflammatory markers measured in blood (C-reactive protein (CRP), tumor necrosis factor alpha (TNF-α), interleukin (IL)-6, IL-8, IL-10), blood creatine kinase activity (CK) as a marker of muscle damage and serum cortisol). Other outcomes include body mass, height, body mass index (BMI), total and regional fat mass, lean mass and body fat, RMR, number of steps/day and time spent at sedentary, light, moderate, vigorous and moderate-to-vigorous PA, total daily energy intake and expenditure, daily intake of carbohydrate, fat, protein, vitamin A, vitamin C, vitamin D, vitamin E, selenium, zinc and magnesium, VO_2max_, knee extensors’ (KE) maximal eccentric and concentric peak torque and DOMS.

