### Exercise protocol

Participants will perform a protocol consisting of 300 eccentric unilateral maximal contractions (20 sets, 15 repetitions/set, 30-s rest between sets) of the quadriceps muscles on an isokinetic dynamometer (Cybex 770, USA) at a speed of 30°/s. A different limb will be used in each trial. Before the protocol a standard warm up will precede involving 8-min cycling on a cycle ergometer (Monark 834, 154 ERGOMED C, Sundbyberg, Sweden) at a speed of 70 rpm/min and at 50 W, followed by 5-min stretching exercises. KE will be isolated using straps in the shoulders, hips and thigh. This protocol has been described in the literature to effectively induce a significant level of skeletal muscle damage and myofibrillar disruption as documented with electron microscopy and immunohistochemistry [30, 31].

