### Statistical analyses and Power calculation

A preliminary power analysis (based on previous studies that used NAC administration to investigate its effects on EIMD), using the G*Power 3.0.10 program, showed that a minimum number of 10 participants per group is needed to obtain statistical meaningful results among repeated measurements [30]. Specifically, power calculation was performed for a two-way repeated-measures analysis of variance (ANOVA), within-between interaction test and input variables included: effect size, 0.55; α error, 0.05; power, 0.95; number of groups (LR and HR), 2; correlation among repeated measures, 0.5 and non-sphericity correction, 1. However, the total number of participants depends also on potential dropouts according to the following formula: *n* ’  = n/(1 − d) [55].

Thus, the final number of participants to be recruited with a dropout rate of 15% would be *n*’ = 10/(1–0.15) = 11.8. Therefore, ≥ 12 participants per group (LR vs HR) will be selected from the initial sample (*N* = 40–60) via k-means clustering to participate in the clinical trial (NAC vs placebo).

A k-means cluster analysis will be utilized to efficiently define two separate groups of subjects (LR and HR groups) from the total sample (*N* = 40–60), based on the SCs content of their vastus lateralis muscle of their dominant leg [24]. This type of analysis requires a relatively large initial sample size (*N* = ≥ 40), is a form of partitional clustering and is a multivariate method used to identify homogeneous groups (i.e., clusters) of cases based on a common trait [29, 56].

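### The biopsy that defines HR and LR should be kept out of the time factor for satellite-cell outcomes: if it is used as a time level or reference, regression to the mean biases the time effects and the HR-versus-LR comparison

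*Protocol article*

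**What the plan says.** Under Study overview and design, each volunteer gives one resting biopsy from the vastus lateralis of the dominant limb and, "based on its SCs content will be stratified to either high (HR) or low (LR) respondents". The method is fixed: "Participants will be stratified as HR or LR using a K-means cluster analysis". Under Statistical analyses and Power calculation, 12 or more "participants per group (LR vs HR) will be selected from the initial sample" of 40 to 60; how they are picked within a cluster is not stated.

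The grouping variable is also an outcome. The outcome list begins: "The primary outcomes of the study are the SCs-specific markers measured in muscle", and it names Pax7+ and MyoD+ cells by fiber type.

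The sampling times are described in two ways. The abstract says that in both trials "muscle biopsies will be collected, and muscle performance and soreness will be measured at baseline, pre-exercise, 2 and 8 days post exercise". Study overview and design describes the baseline once, ahead of the trials, and then gives the within-trial biopsies as taken "before the exercise protocol (pre-exercise sampling) as well as at 2 and 8 days post exercise". Muscle biopsy sampling also treats those three as following the baseline.

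The statistics section plans a two-way repeated-measures ANOVA for time and trial effects in the LR and HR groups, with Bonferroni-corrected pairwise comparisons. It names neither the levels of the time factor nor a reference time for Pax7. Baseline is the stated reference only for mRNA fold changes (Quantitative RT-PCR). Under Exercise protocol: "A different limb will be used in each trial".

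**The concern.** A group formed by cutting a single noisy measurement contains, on its high side, people whose error happened to be positive and, on its low side, people whose error happened to be negative. The next biopsy carries fresh error, so the high group falls on average and the low group rises. If the first biopsy is a level of the time factor, or the reference for change, this appears as a time effect in each group and as a group-by-time difference.

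The abstract's discussion names as an expected finding whether the muscle's capacity to regenerate depends on its basal satellite-cell content. That question is answered by comparing HR and LR over time, which is where the artefact falls. The baseline is also likely to be used: the pre-exercise biopsy follows seven days of loading, so baseline is the only value before any supplement.

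A second problem rests on the same condition. The baseline comes from the dominant limb and the limbs alternate between trials. In the trial on the non-dominant limb, change from baseline would therefore mix time with a difference between limbs.

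**Working it through.** The plan has no figure of its own for this point. The inputs taken from it are the initial sample (40 to 60), two clusters by k-means on one measurement, and 12 per group (10/(1 − 0.15) = 11.8, rounded up). The reliability of a single Pax7 biopsy is not given and is assumed here to lie between 0.5 and 0.9. The planning correlation of 0.5 among repeated measures is at the lower end of that range, but it is not a measured reliability.

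**Step 1, by formula.** With total SD 1, expected drift = (1 − reliability) × mean standardised baseline in the selected group. For an even split of a normal variable that mean is 0.798. This gives:
- reliability 0.5: 0.5 × 0.798 = 0.399 SD
- reliability 0.7: 0.3 × 0.798 = 0.239 SD
- reliability 0.8: 0.2 × 0.798 = 0.160 SD
- reliability 0.9: 0.1 × 0.798 = 0.080 SD

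**Step 2, by simulation.** True values have variance equal to the reliability. Each biopsy has independent error and nothing truly changes. K-means is run on the baseline of N = 40 or 60, and 12 are drawn at random from each cluster (about 1,370 to 1,500 usable runs per setting). The placebo-trial series is tested by repeated-measures ANOVA at 0.05, first with baseline as one of four levels and then without it.

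| Reliability (assumed) | Drift, LR up and HR down (SD) | False time effect per group, baseline in | False group-by-time, baseline in | False group-by-time, baseline out |
|---|---|---|---|---|
| 0.5 | 0.41 | 28–29% | 54% | 4–5% |
| 0.7 | 0.24–0.25 | 16–19% | 32–34% | 5–6% |
| 0.8 | 0.16 | 11–14% | 21–22% | 5–6% |
| 0.9 | 0.08–0.09 | 9% | 12–13% | 4–5% |

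**Step 3, the single contrast from baseline to pre-exercise.** A two-sample t-test of HR against LR change, unadjusted, is falsely significant in about 55% of trials at reliability 0.5, 23% at 0.8, and 13% to 15% at 0.9. When change is measured from pre-exercise the rate is about 5%.

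**Step 4, with the planned Bonferroni correction.** Four levels give six pairs, so each contrast is allowed 0.05/6 = 0.8%. Within HR, at reliability 0.5 to 0.8, the baseline-to-pre-exercise contrast is falsely significant in about 10% to 4% of trials. At least one of the three contrasts with baseline is falsely significant in about 24% to 10%, where the allowance is at most 3 × 0.8% = 2.5%. The inflation is smaller but remains.

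**Step 5, the randomised contrast.** NAC and placebo series were generated for the same people under the same classification. The mean NAC-minus-placebo difference was 0.00 ± 0.01 SD in both groups, so the selection error cancels.

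**The case against.** The strongest reply is that the article nowhere states that baseline is a level of the time factor for Pax7. The design section's three within-trial times fit an analysis that starts at pre-exercise, and such an analysis is free of the problem. The time levels may be named in a full protocol or analysis plan not shown here, and the flowchart figure is missing. The abstract's sentence, read literally, also gives each trial its own baseline; a second-trial baseline classified nobody and would carry no selection error. All of this stands, and it makes the point conditional. It does not remove it: the abstract does list baseline beside the other times, and nothing shown excludes it.

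Three stronger readings are tempting and are not supported:
- **The NAC effect is biased.** It is not. Both trials share one classification, and the article's stated objective and hypothesis concern NAC.
- **The artefact creates the pattern the trial expects.** The design section's rationale ties myogenic potential directly to basal content, which suggests a larger response in high-content muscle. The drift runs the other way and would tend to mask that pattern.
- **The false-positive rates are far higher because the most extreme 12 per cluster are taken.** That would worsen every figure, but the article does not say that selection works this way.

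It is also fair to object that the sizes rest on an assumed reliability and that the figures in Step 3 are unadjusted. They should be read as a range.

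**Conclusion.** The concern holds conditionally. If the classifying baseline is used as a time level or reference for satellite-cell outcomes, LR will drift up and HR down without any true change, and both the non-randomised time effects and the HR-versus-LR comparison will be biased. The direction is certain under that condition. The size depends on the reliability assumed, on random selection within clusters, and on independent errors between biopsies. Even at reliability 0.9, the false HR-versus-LR rate stays at more than twice the nominal 5%.

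Separately from that condition, the abstract and the design section disagree on whether baseline is sampled once or in each trial, and this needs correcting in any case.

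**What to change.** 1. Reconcile the abstract with Study overview and design on whether baseline is sampled once, before both trials, or in each trial.
2. State that the classifying biopsy is used only to form HR and LR, and is neither a time level nor the reference for satellite-cell outcomes.
3. Run the repeated factor for these outcomes over pre-exercise, day 2 and day 8. This also removes the between-limb component from change scores.
4. Judge the HR and LR time courses from the placebo trial, with its own pre-exercise biopsy as reference. Judge NAC as the NAC-placebo difference at each time.

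The cost is wording only: the pre-exercise biopsies are already planned and the sample size does not change. One time level is lost for the satellite-cell outcomes. Any effect of the loading phase is then read from the NAC-placebo difference at pre-exercise instead of from change since baseline.
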